### Data collection

At baseline, patients will be asked to fill in digital or paper questionnaires before the start of the treatment, and after 4 and 26 weeks follow-up. After 12 weeks, patients will be called by the investigators to collect data about global perceived recovery, pain severity, and costs (Table 1).

**Table 1 T1:** Overview of data collection

Primary outcomes		
Shoulder-specific function	Simple Shoulder Test	Baseline, 4 and 26 weeks
Pain severity	11-point numerical rating scale	Baseline, 4, 12 and 26 weeks

**Secondary outcomes**		

Global perceived recovery	7-point Likert scale	4, 12 and 26 weeks
Primary functional problem	11-point numerical rating scale	Baseline, 4 and 26 weeks

**Economic evaluation**		

Costs	Cost diary	4, 12 and 26 weeks
Health related quality of life	EuroQol	Baseline, 4 and 26 weeks

**Other**		

Demographic data	Questionnaire	Baseline
General health	Short-form 36	Baseline

The baseline questionnaire will include questions about socio-demographic characteristics (e.g. age, gender, and marital status), pain severity, shoulder-specific function, primary functional problem, health related quality of life and general health. General health will be evaluated with the Short-Form 36 (SF-36) [24]. This questionnaire consists of 36 questions that can be aggregated to form eight subscales (physical functioning, mental health, general health perceptions, pain, role limitations physical, role limitations emotional, social functioning, and vitality) and two sum scales (physical and mental component scales). The scores on all subscales range from 0-100, with higher scores indicating better outcomes. It is a widely used measurement instrument with satisfactory validity, reproducibility and responsiveness to change [25]. The Dutch translation has been found to be sufficiently valid [26].

### Outcome measures

The primary outcome measures will be:

**The Simple Shoulder Test (SST) **[27] measuring shoulder function. The SST will measure gains and losses of function over time through a series of 12 questions with dichotomous "yes" or "no" response options. More scores on yes relates to less pain and less disability of the shoulder. The SST has been found to be sufficiently valid, reliable and responsive [28,29].

**The numerical rating scale (NRS) **measuring pain severity. The NRS (0 = no pain to 10 = worst imaginable pain) is well-accepted in clinical research with good validity and reliability [30-32].

Secondary outcome measures include:

**Global perceived recovery**, measured by self-assessment on a 7-point Likert scale ranging from "completely recovered to "worse than ever" [33]. This will be dichotomized into success (complete and much recovered) and non-success (slightly recovered, no change, slightly worse, much worse, and worse than ever).

**Perceived recovery from a primary functional problem**, measured by an 11-point NRS. Prior to the treatment programme, the patients will select one functional activity that often occurs and cannot be avoided. The patient will be asked to describe the activity as specific as possible and wherever possible to quantify the activity in terms of time, distance, weight lifted, and so on. Beurskens et al. investigated the value of this instrument in patients with low back pain, but used a more complex procedure compared to our pragmatic approach [34]. They concluded that the responsiveness is good and changes in function problems were displayed properly.

### Blinding

The treating PTs and patients cannot be blinded for the treatment allocation because of the knowledge of receiving the modality. The investigators, who will conduct the data collection and data entry, will not be blinded. However, almost all outcome measures will be collected using questionnaires without personal contact with the patient. The participating statistician will perform the analyses blinded for treatment allocation.

### Sample size

Power calculations, based on the studies carried out by Santamato et al. [35] and Tashjian et al. [36] were performed for the 2 main outcomes (power 0.95; alpha 0.05). To detect a clinically relevant mean difference between the two treatment groups of 2 points on the SST [36] (standard deviation [SD] 2), 26 patients are needed per group. To detect a clinically relevant mean difference of 2 points (SD 3) for pain (11-point NRS) [35], 2 groups of 59 patients are needed. Anticipating a potential drop-out of 15%, 70 participants per treatment group (total n = 140) will be recruited.

### Data-analysis

Baseline characteristics of the two treatment groups will be compared regarding the main prognostic characteristics. The primary analysis will be on an intention-to-treat basis. The data will be analyzed in a linear mixed model with measurements at baseline, 4, 12 and 26 weeks. In this model, the effect of the interaction is time by treatment interaction. The included levels will be; repeated measures (i.e. time), patient, PT, and PT practice. The treatment effects between baseline measurement and follow-up will be calculated between the two treatment groups with a 95% confidence interval. If prognostic factors are unevenly distributed, multivariate analysis will be used to correct for the differences between the groups.

The influence of deviations on the treatment protocol will be evaluated using a per protocol analysis. A deviation of the protocol is defined as not receiving treatment after allocation, withdrawal from therapy after one to three visits and not being treated according to patient's treatment allocation.

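### As worded, the primary mixed model compares change from baseline, which is valid but less precise than prespecified adjustment for a baseline measured before allocation

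*Protocol article*

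**What the plan says.** The Data-analysis section of the protocol article makes baseline one of the modelled occasions: "The data will be analyzed in a linear mixed model with measurements at baseline, 4, 12 and 26 weeks". It names the effect of interest: "In this model, the effect of the interaction is time by treatment interaction". It describes what will be reported: "The treatment effects between baseline measurement and follow-up will be calculated between the two treatment groups with a 95% confidence interval". Covariate adjustment appears only as a conditional step: "If prognostic factors are unevenly distributed, multivariate analysis will be used to correct for the differences between the groups".

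The Sample size section uses power 0.95 and alpha 0.05 for both primary outcomes. For pain it reads "To detect a clinically relevant mean difference of 2 points (SD 3) for pain (11-point NRS"), giving 59 per group. For function it reads "2 points on the SST [36] (standard deviation [SD] 2), 26 patients are needed per group". With 15% drop-out, 70 per group are to be recruited. The section does not say whether either SD belongs to a single score or to a change.

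Under Recruitment of patients, the baseline questionnaires are completed before the second consult, and the allocation envelope is opened at that consult after consent. Table 1 schedules pain at baseline, 4, 12 and 26 weeks, and SST at baseline, 4 and 26 weeks only.

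**The concern.** Taken together, these statements describe a between-arm difference in change from baseline. Baseline precedes allocation, so the two arms have the same expected baseline mean. A model that still estimates a baseline difference and subtracts it from the follow-up difference adds the noise of the baseline measurement to the effect. Given a chance baseline imbalance, the change contrast also favours the arm that started worse.

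Adjusting for baseline, or constraining the baseline means to be equal, avoids both problems. At stake are the width of the confidence intervals for both primary outcomes and, under one reading of the planning SD, whether pain reaches its planned power. The conditional adjustment step does not supply this gain. It depends on seeing an imbalance and does not name the outcome's own baseline, whereas the gain comes from the correlation between baseline and follow-up and exists with or without imbalance.

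**Working it through.** **Inputs from the article.** Pain: difference 2, SD 3. SST: difference 2, SD 2. Alpha 0.05, power 0.95, drop-out 15%. Sidedness is not stated; two-sided reproduces the figures.

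**Assumed input.** ρ, the baseline to follow-up correlation. The article gives none, so a range is shown.

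**1. The plan's own sample size.** n per group = 2(1.960 + 1.645)²(SD/difference)².
- SST: 2 × 12.99 × (2/2)² = 25.99, so 26.
- Pain: 2 × 12.99 × (3/2)² = 58.5, so 59.
- Drop-out: 59/0.85 = 69.4, so 70 per group and 140 in total.

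All stated figures reproduce.

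**2. Precision of the two analyses.** Let σ be the SD of a single score, equal at baseline and follow-up, with complete data and separate baseline means per arm.
- Change contrast: variance per patient 2(1−ρ)σ².
- Baseline-adjusted contrast: variance per patient (1−ρ²)σ².
- Ratio adjusted/change = (1−ρ²)/[2(1−ρ)] = (1+ρ)/2, so the information lost is 1 − (1+ρ)/2 = (1−ρ)/2.

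| ρ | 0.2 | 0.3 | 0.4 | 0.5 | 0.6 | 0.7 | 0.8 |
|---|---|---|---|---|---|---|---|
| Information lost | 40% | 35% | 30% | 25% | 20% | 15% | 10% |

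**3. Drop-out.** The variances of the two mixed models (free against common baseline mean) were also computed with 15% missing the last visit and equal correlations between visits. The loss at that visit is about 36%, 22% and 18% at ρ = 0.2, 0.5 and 0.6, slightly below the complete-data values.

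**4. Pain power, if SD 3 is a single-score SD.** 59 per arm, two-sided t-test. Change SD = 3√[2(1−ρ)]; adjusted SD = 3√(1−ρ²).

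| ρ | Change SD | Power, change | Adjusted SD | Power, adjusted |
|---|---|---|---|---|
| 0.2 | 3.79 | 0.81 | 2.94 | 0.96 |
| 0.3 | 3.55 | 0.86 | 2.86 | 0.96 |
| 0.4 | 3.29 | 0.91 | 2.75 | 0.97 |
| 0.5 | 3.00 | 0.95 | 2.60 | 0.99 |
| 0.6 | 2.68 | 0.98 | 2.40 | 0.99 |

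**5. Pain power, if SD 3 is already a change SD.** The change contrast keeps 0.95. The adjusted SD is 3√[(1+ρ)/2], which gives about 0.996 at ρ = 0.2, 0.98 at 0.6 and 0.97 at 0.8.

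**6. SST power, 59 per arm.** If SD 2 is a single-score SD, the change contrast has power 0.97 at ρ = 0, 0.99 at 0.2 and 0.995 at 0.3. If SD 2 is a change SD, power exceeds 0.99. It stays above 0.95 in every case.

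**The case against.** Several points on the other side are fair.

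**The baseline means are not said to be free.** The article never names a treatment main effect or separate baseline means per arm. A model with a common baseline mean would also fit its sentences, and a condensed article may leave such coding to a fuller document. This stands as a limit: the change-score reading is the plain one, especially since effects are described as running from baseline to follow-up, but it is an inference.

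**The size of the loss.** A reader might take a loss of 20 to 40% as established. It corresponds to ρ between 0.2 and 0.6, which the article does not give. At ρ = 0.8 the loss is 10%.

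**Power.** A reader might infer that the trial is underpowered. The documents do not support that. The shortfall needs SD 3 to be a single-score SD and ρ below 0.5, and it concerns pain only. Even then power is above 0.80 at ρ = 0.2.

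**Bias.** A reader might infer that the planned comparison is biased or its intervals invalid. Under randomisation neither is true. Regression to the mean matters only conditional on a chance imbalance, and the plan does provide for adjustment when prognostic factors differ. That provision is a partial answer: it is data-dependent and does not name the outcome's baseline, so it leaves the precision loss in place.

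**Conclusion.** The point holds as a loss of efficiency. On the plain reading, the primary effect is a difference in change from baseline, and (1−ρ)/2 of the available information is given up compared with baseline adjustment. That expression is exact for complete data, equal variances and unconstrained baseline means, and it is positive for every ρ below 1. Its value depends on a correlation that the article does not report. The consequence for the stated pain power depends further on what the SD of 3 describes. At every ρ from 0.2 to 0.8 examined here, adjustment keeps pain power at 0.95 or more under both readings of that SD; the change contrast does so only if SD 3 is a change SD or ρ is about 0.5 or higher. The planned analysis remains valid, so this is a recommended improvement and clarification.

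**What to change.** Prespecify one of two models, to be used regardless of any observed imbalance:

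- The same mixed model with baseline means constrained equal across arms: time effects plus treatment-by-follow-up terms, and no treatment effect at baseline.
- A mixed model of follow-up values only (4, 12 and 26 weeks for pain; 4 and 26 weeks for SST), with the outcome's own baseline value as a covariate.

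Report the adjusted between-arm difference with its 95% confidence interval at each follow-up. The two options are close but not identical when follow-up data are missing: a patient with a baseline value and no follow-up contributes to the first and not to the second. It would also help to state whether the planning SDs are for single scores or for change.

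The cost is a sentence or two in the analysis section. No new data or patients are needed.

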### Economic evaluation from a societal perspective

The economic evaluation will be conducted from a societal perspective. Both a cost-effectiveness and cost-utility analysis will be performed. Shoulder function (SST) and pain severity (NRS) will be primary outcomes in the cost-effectiveness analysis. Health-related quality of life will be measured with the EuroQol (EQ-5D) [37]. This questionnaire assesses 5 dimensions (mobility, self-care, usual activities, pain/discomfort and anxiety/depression) on a 3-point scale; no problems, moderate problems and severe problems. The questionnaire is appropriate for estimating quality-adjusted life-years (QALYs), and can be used for cost-utility analysis. The total score is expressed in utilities according to the Dolan model [38]. QALYs will be calculated by multiplying the utility of a health state by the time spent in this health state, based on the Dutch valuation tariff [39].

Direct and indirect costs will be measured by means of self-completed cost diaries [40]. The following costs will be evaluated: I) health care costs (e.g. primary care, medical specialist care, prescription of medication, and hospitalization); II) patient costs (out-of-pocket expenses, such as over-the-counter medication and CAM); and III) costs of loss of productivity (work absenteeism).

Costs will be valued according to the guidelines published in the updated handbook for economic evaluation in the Netherlands [41]. For paid labour, the costs will be calculated, using both the human capital approach and the friction cost approach. The incremental costs from the intervention group over the usual care group will be compared to incremental outcomes. The incremental cost-effectiveness ratios (ICER) will be calculated with the mean differences in costs and effects. To calculate the mean differences in costs and to analyse the uncertainty around the ICERs, the bias-corrected percentile bootstrapping method (5,000 replications) will be used. The uncertainties around the ICERs will be presented in a cost-effectiveness plane. Finally, the probability that usual care with the particular tape technique is cost-effective in comparison to usual care for various thresholds decision makers are willing to pay to gain one extra unit of effect will be presented on a cost-effectiveness acceptability curve.

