Three studies have examined the clinical effects of taping patients with SAIS using leukotape in combination with fixomull stretch (BSN medical^®^) [12-14]. In a pilot study of 22 patients with unilateral shoulder pain of more than six weeks, Miller et al. [12] compared taping as an adjunct to usual physical therapy with usual physical therapy alone. They found a strong trend toward reduced pain and improved function in favor of scapular taping at two weeks. The magnitude of these differences was reduced at a follow-up at six weeks. Case studies of taping patients with SAIS have been published by Host et al. [13] and Shamus and Shamus [14]. Both studies found a reduction in pain and an improvement of function. In sum, the effects in pain relief and improving shoulder function due to shoulder taping looks promising. However, study samples were small or had no control group. In addition, tape techniques vary and we must conclude that the evidence for its usefulness is still limited. Therefore, the primary aim of this study is to assess the effectiveness and cost-effectiveness of usual physical therapy care in combination with one particular tape technique for subacromial impingement syndrome of the shoulder compared to usual physical therapy care alone in a primary health care setting.

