### Tape method

Patients who are allocated to usual physical therapy in combination with tape will be treated at the end of each treatment session for at least 4 weeks by a modified tape technique after Shamus and Shamus [14]. In this technique, the arm of the patient lays on the treatment table, with the shoulder in 80° abduction in the plane of the scapula (Figure 2). Two strips of rigid tape (leukotape, BSN medical^®^) will be placed upon two strips of elastic tape (fixomull stretch, BSN medical^®^) without tension. When the arm of the patient is brought back to a relaxed position along the body, the arm will be slightly abducted from the body (approximately 10°) due to the tension of the tape (Figure 3). The tape will be worn for a minimum of 2 and a maximum of 7 days. Tape will be worn for short periods (2-3 days) for patients with severe pain and at the beginning of the tape period, and longer for patients with less pain and who are familiar with wearing the tape. In addition, patients with severe pain will be taped with the shoulder in less abduction (50-70°) so that the tape produces less tension when the arm is in the relaxed position. At least one to two days before the next treatment, the tape will be removed by the patient in order to let the skin recover from the tape. The PT is free to determine the abduction angle of the shoulder in which the shoulder will be taped, the exact days the tape will be worn and the number of treatments per week in order to reflect clinical practice. During the first 4 weeks, the treatment with tape will be stopped if the patient is free of pain, allergic to tape or reports a substantial increase in complaints because of the tape.

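### EQ-5D is skipped at the 12-week call, so the QALY difference over weeks 4 to 26 rests on interpolation and could be too large or too small

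*Protocol article*

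**What the plan says.** Under Economic evaluation from a societal perspective, the protocol article plans a cost-utility analysis in which "QALYs will be calculated by multiplying the utility of a health state by the time spent in this health state". In the economic evaluation block of Table 1, the EuroQol is scheduled at "Baseline, 4 and 26 weeks", whereas the cost diary is scheduled at "4, 12 and 26 weeks". The Data collection section agrees with the table: "After 12 weeks, patients will be called by the investigators to collect data about global perceived recovery, pain severity, and costs". The Abstract and the Design section describe measurement at 4, 12 and 26 weeks in general terms, but the EuroQol row and the list of items for the call show that no utility is taken at week 12.

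Two further statements bear on the likely course of an effect. Under Tape method, patients in the tape group "will be treated at the end of each treatment session for at least 4 weeks". In the Background, the article says of a 22-patient pilot of scapular taping, which showed a trend in pain and function at two weeks: "The magnitude of these differences was reduced at a follow-up at six weeks".

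On estimation, the article says "The incremental cost-effectiveness ratios (ICER) will be calculated with the mean differences in costs and effects".

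**The concern.** A QALY is an area under a utility curve. With readings at 0, 4 and 26 weeks, the curve has no interior point for 22 of 26 weeks (85%). The week-4 reading falls at the end of the minimum taping period, when an effect may well be near its height. If the effect then fades quickly, a straight line from week 4 to week 26 credits benefit that has already gone. If it persists and fades late, the same line removes benefit that was there.

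The QALY difference is the denominator of the cost-utility ratio, so an error in it passes directly into the ICER. Costs are observed at week 12 and utilities are not, so the numerator is followed more closely than the denominator. The gap is a matter of data collection: an analysis plan can choose how to bridge it but cannot fill it.

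**Working it through.** **Inputs from the protocol article.** EQ-5D at 0, 4 and 26 weeks; a 12-week call that already takes place; a 26-week horizon. The article states no QALY figure, so there is none to reproduce.

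**Assumptions, not in the documents.** The between-group utility difference is 0 at baseline, rises linearly to d at week 4, and is 0 at week 26. Interpolation between readings is linear. The size of d cancels in the ratios.

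**Trapezoid weights, in weeks.** Each reading gets half of each adjoining interval.
- 0/4/26: week 0 = 4/2 = 2; week 4 = (4 + 22)/2 = 13; week 26 = 22/2 = 11. Sum 26.
- 0/4/12/26: week 0 = 2; week 4 = (4 + 8)/2 = 6; week 12 = (8 + 14)/2 = 11; week 26 = 14/2 = 7. Sum 26.

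Week 4 thus carries exactly half the weight under the planned schedule, and 6 of 26 weeks once week 12 is added.

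**True area for a linear fade from d at week 4 to zero at week T:** 2d + (T − 4)d/2. For T = 12 this is 2d + 4d = 6d.

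**True area if d holds to week 12 and then falls linearly to zero at week 26:** 2d + 8d + 14d/2 = 17d.

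**Area under the planned schedule in all these cases:** 13d.

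| Course after week 4 | True area | 0/4/26 | Ratio | 0/4/12/26 | Ratio |
|---|---|---|---|---|---|
| gone by week 8 | 4d | 13d | 3.25 | 6d | 1.50 |
| gone by week 12 | 6d | 13d | 2.17 | 6d | 1.00 |
| gone by week 16 | 8d | 13d | 1.63 | 9.67d | 1.21 |
| gone by week 20 | 10d | 13d | 1.30 | 11.5d | 1.15 |
| gone by week 26 | 13d | 13d | 1.00 | 13d | 1.00 |
| held to week 12, zero at week 26 | 17d | 13d | 0.76 | 17d | 1.00 |

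The overstatement is exactly twofold when the effect is gone by week 13: 13/(2 + 9/2) = 13/6.5 = 2.00.

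**In QALYs, with d = 0.10 for illustration.** The planned schedule gives 13 × 0.10/52 = 0.0250. The true value is 6 × 0.10/52 = 0.0115 for a fade by week 12, and 17 × 0.10/52 = 0.0327 for the effect held to week 12.

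**Effect on the ICER, cost difference unchanged.** It becomes 6/13 = 0.46 of its true value in the first case and 17/13 = 1.31 times its true value in the second.

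**Dependence on the interpolation rule.** For a fade by week 12 (true 6d), linear interpolation gives 13d, carrying week 4 forward to week 26 gives 22d, and applying each reading to the interval before it gives 4d. The rule alone can change the direction of the error.

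**The case against.** A reader might infer that the plan will more than double the QALY gain. The documents do not support that. It requires linear interpolation, a peak at week 4, no difference at week 26 and a fade complete before week 13, all at once. The article fixes no interpolation rule and gives no utility time course. The pilot had 22 patients, measured pain and function rather than utility, and found a difference that was smaller at six weeks, not absent. Taping may also continue beyond four weeks. These objections stand: an early fade is plausible but not established, and the error can go either way.

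A reader might also infer that the incremental QALY will be unadjusted for baseline utility. The article says only mean differences. The Data-analysis section adds "If prognostic factors are unevenly distributed, multivariate analysis will be used to correct for the differences between the groups", without saying whether this extends to the economic evaluation. Baseline adjustment is a detail that an article may leave to a fuller document, so silence here is no fault.

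Two practical objections have some weight. The primary outcomes, function and pain, also serve as the primary effects in the cost-effectiveness analysis and do not use the EQ-5D. And the 12-week contact is a telephone call by investigators who, under Blinding, are not blinded, whereas the other readings are by questionnaire. The first limits the importance of the point. The second is a real but small cost, already accepted for pain at the same call.

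None of this removes the core: utility is not measured between weeks 4 and 26, although a contact exists at which it could be.

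**Conclusion.** The point holds as a weakness in the measurement schedule, confined to the cost-utility analysis. Under linear interpolation with a week-4 peak, the reported QALY difference is about 2.2 times the true one if the effect is gone by week 12, and 0.76 of it if the effect holds to week 12 and fades by week 26. Across the courses tabulated, the ratio runs from 0.76 to 3.25. These figures rest on assumed courses and on an interpolation rule that the article does not state, so they show how sensitive the result is and do not predict a bias. A week-12 reading brings the estimate closer to the truth in every tabulated course where the planned schedule errs, and makes it exact in the two main cases.

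**What to change.** Add the five EQ-5D items to the existing 12-week call, amend the EuroQol row of Table 1 and the Data collection section to match, and compute QALYs as the area under the curve from 0, 4, 12 and 26 weeks with the interpolation rule stated. The cost is a few more minutes per call and a change of mode, with an unblinded caller, at that one time point. No visit, sample size or treatment changes.

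If the call cannot be extended, state the interpolation rule and report a sensitivity analysis over early-fade and late-fade courses. This shows the uncertainty but does not remove it.

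As a secondary, optional step, estimate the incremental QALY with the baseline EQ-5D, which is already collected, as a covariate within each bootstrap replicate. A chance baseline difference b that persisted for 26 weeks would otherwise add 26b/52 = 0.5b QALY. This costs only a small change to the analysis code.

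### The economic evaluation names no adjustment for baseline EQ-5D in the incremental QALYs and does not tie the SST and NRS increments to the trial's mixed model

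*Protocol article*

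**What the plan says.** The Protocol article, section Economic evaluation from a societal perspective, gives the estimator: "The incremental cost-effectiveness ratios (ICER) will be calculated with the mean differences in costs and effects". The next sentence gives the method of inference: "To calculate the mean differences in costs and to analyse the uncertainty around the ICERs, the bias-corrected percentile bootstrapping method", with 5,000 replications. The section mentions no regression, covariate or baseline term.

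On utilities it says "QALYs will be calculated by multiplying the utility of a health state by the time spent in this health state". The economic block of Table 1 lists the instrument as "EuroQol Baseline, 4 and 26 weeks", so a baseline utility will be available for use as a covariate.

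On clinical effects it says "Shoulder function (SST) and pain severity (NRS) will be primary outcomes in the cost-effectiveness analysis". These are also the trial's two primary outcomes. Data-analysis treats them differently: "The data will be analyzed in a linear mixed model with measurements at baseline, 4, 12 and 26 weeks". The treatment effect there is a time-by-treatment contrast from baseline to follow-up, and "The included levels will be; repeated measures (i.e. time), patient, PT, and PT practice". Data-analysis also provides for multivariable correction if prognostic factors turn out unbalanced. Neither section says whether that model or that correction extends to the economic analysis.

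**The concern.** A QALY is a single total per patient over 26 weeks and has no baseline value of its own. A change score therefore cannot remove a baseline difference, and a repeated-measures model with baseline as one of the occasions does not naturally do so either. The usual route is to regress the QALY on arm and baseline utility, and the section gives baseline EQ-5D no such role. Without it, the cost-utility plane and acceptability curve depend partly on which arm happened to start with better utility, and the QALY difference is estimated with avoidable noise.

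For SST and NRS the stake is consistency. If the ICER effects are computed outside the mixed model, one trial could report two treatment effects for the same outcome. Readers could not tell whether the gap reflects the treatment or the choice of estimator.

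**Working it through.** **Inputs from the document.** EQ-5D at weeks 0, 4 and 26 (Table 1). Analysable patients: 59 per group (Sample size). That figure reproduces: 2 × (1.960 + 1.645)² × 3² / 2² = 58.5, rounded up to 59; and 59 / 0.85 = 69.4, rounded up to 70.

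**Assumptions, because the document is silent.** Utility SD 0.20 at each visit; the same correlation r between any two visits, 0.5 with a range of 0.3 to 0.7; QALYs by the trapezoid rule.

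**QALY weights.** Week 0: (4/2)/52 = 2/52. Week 4: (26/2)/52 = 13/52. Week 26: (22/2)/52 = 11/52. They sum to 0.5 year. Baseline itself carries only 2/26 = 7.7% of the weight, so most of any shift comes through the correlation of later utilities with baseline.

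**Shift from baseline imbalance.** Slope of the QALY on baseline utility: c = 2/52 + r × 24/52. At r = 0.5, c = 0.0385 + 0.5 × 0.4615 = 0.269. The standard error (SE) of the baseline difference is 0.20 × √(2/59) = 0.0368. A one-SE imbalance therefore shifts the QALY difference by 0.269 × 0.0368 = 0.0099. For scale, a utility gain of 0.05 held over all 26 weeks is 0.05 × 0.5 = 0.025 QALY, and the shift is 40% of that.

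**Precision.** Unadjusted variance factor: v = (2² + 13² + 11²)/52² + 2r × (2×13 + 2×11 + 13×11)/52² = 0.1087 + 2r × 0.0706. At r = 0.5, v = 0.1794 and the SE is √0.1794 × 0.0368 = 0.0156. The share of variance explained by baseline is c²/v = 0.0725/0.1794 = 0.404. The adjusted SE is 0.0156 × √(1 − 0.404) = 0.0120.

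| r | one-SE shift | SE unadjusted | SE adjusted | variance reduction |
|---|---|---|---|---|
| 0.3 | 0.0065 | 0.0143 | 0.0127 | 21% |
| 0.5 | 0.0099 | 0.0156 | 0.0120 | 40% |
| 0.7 | 0.0133 | 0.0168 | 0.0102 | 63% |

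Shifts and SEs scale with the SD. At r = 0.5, SDs of 0.15 and 0.30 give one-SE shifts of 0.0074 and 0.0149. The variance reduction depends on neither the SD nor the sample size. With 70 per arm, SD 0.20 and r = 0.5, the shift is 0.0091 and the SE falls from 0.0143 to 0.0111.

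**SST and NRS.** A difference in final scores and a difference in changes from baseline differ by exactly the baseline difference. Taking the Sample size SDs (2 for SST, 3 for NRS) as baseline SDs, which is an assumption, one SE of baseline difference with 59 per arm is 2 × √(2/59) = 0.37 SST points and 3 × √(2/59) = 0.55 NRS points. Against the 2-point target differences these are 18% and 28%. This is the gap that could arise if the ICER used final scores while the clinical result used the baseline-to-follow-up contrast.

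**The case against.** The strongest reply is that the section is silent on adjustment and does not reject it. A reader might infer that the ICERs will use raw, unadjusted differences. The text does not say so: a mean difference can be a change-score or covariate-adjusted difference, and a condensed article may leave covariates to a fuller plan. This stands as a limit on the claim. It does not remove the point, because the article does fix the estimator, the bootstrap type and the number of replications, and the cost-utility analysis as printed has no baseline term. The conditional correction in Data-analysis is not excluded from the economic analysis, but it depends on what imbalance is seen and does not name EQ-5D.

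Three other inferences go too far:

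- That the QALY result is biased. Randomisation makes the unadjusted difference unbiased on average, and its interval already allows for chance imbalance: the one-SE shift is 0.0099/0.0156 = 0.64 of the unadjusted SE. Conditional imbalance and lost precision are two views of one loss and should not be counted twice.
- That the economic and clinical SST and NRS effects will differ. They can differ, but the ICER might use the model estimates, or mean changes that come close to them. The document excludes neither.
- That the bootstrap ignores practice. The resampling unit is not stated, so nothing can be concluded from the text.

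**Conclusion.** The point holds as a worthwhile tightening of the plan; no error is demonstrated. As printed, the cost-utility analysis gives no role to a baseline covariate that is already scheduled, and the section does not say which SST and NRS effects enter the ICERs. Under the assumed SD and correlation, a quite ordinary baseline imbalance moves incremental QALYs by about 0.010, and adjustment removes about 40% of their variance. The gain depends strongly on the between-visit correlation, which the document does not give, but at 0.3 it is still about a fifth. For SST and NRS the conclusion is only that the two analyses can diverge, by an amount that depends on the unstated definition of the effect.

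**What to change.** State in the economic section that, within each bootstrap replicate:

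1. incremental QALYs are estimated by regression on arm and baseline EQ-5D utility;
2. incremental SST and NRS are the baseline-to-follow-up treatment contrasts from the Data-analysis mixed model. A separate regression on the baseline score would not be that model and would bring back a second effect estimate for each outcome;
3. the cost-effectiveness plane and the acceptability curve are built from these estimates.

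This point does not call for resampling within arm and practice. Treatment allocation issues 10 to 20 envelopes per practice, so such strata would hold about 5 to 10 patients at most. Bootstrapping within strata of size m understates variance by roughly 1/m, here 10% to 20%, and by more in smaller strata.

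The cost is a sentence or two in the plan and slightly more analysis work, mainly refitting the models in each replicate. No new data are needed. Settling it before the data are analysed also avoids a later choice between adjusted and unadjusted ICERs.
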